### Follow-up assessments

The evaluations for the main outcome (eating behaviour) and the secondary outcomes (mindfulness skills, self-compassion, nutritional status, depression and stress) will occur at baseline (T0), immediately after the 8- or 10-week intervention (T1) and at 3 months post-intervention (T2) (*see* Table 1). The outcomes of the practices, unexpected (adverse) effects and maintenance of and adherence to practices will all be evaluated in the T1–T2 intervals. The estimated time for completing the questionnaires and other evaluations is approximately 90 minutes, and the questionnaires will be administered before the beginning of the first and last sessions of each group, as well as at follow-up. For groups G2 and G3, one session will be offered each month to cultivate and strengthen the practice of mindfulness in the group, according to the practices described in each protocol. After the 3-month follow-up, the control group will be offered what is determined to be the most effective intervention, either MB-EAT or MBHP (Table 1).

**Table 1 Tab1:** Overview of measures and corresponding measurement time points

Measure	Target concept	Baseline	T1	T2
BES	Binge eating	x	x	x
BPAAT	Physical activity	x	x	x
DEBQ	Food style	x	x	x
EAT-26	Presence of abnormal eating patterns	x	x	x
HADS	Anxiety and depression symptoms	x	x	x
MAAS	Mindfulness skills	x	x	x
FFQ	Food Frequency Questionnaire	x	x	x
SCS	Self-compassion	x	x	x
Transtheoretical Model	Behaviour change	x	x	x
Feasibility Questionnaire	Feasibility of intervention		x	
Adverse effects questionnaire	Occurrence adverse effects		x	x
Amount of weekly practices	Adherence to practice		x	x
Anthropometry	Change in weight	x	x	x
Basal metabolic rate	Basal metabolism	x	x	x
Body composition	Fat mass and lean mass	x	x	x
BDNF	Brain-derived neurotrophic factor	x	x	x
Cortisol serum	Stress	x	x	x
Fasting blood glucose	Glycaemic control	x	x	x
HbA1c	Haemoglobin A1c	x	x	x
Insulin	Insulin	x	x	x
US-CRP	Ultra-sensitive C-reactive protein	x	x	x
Total cholesterol, fractions and TGL	Lipid profile	x	x	x
Alpha-1-glycoprotein	Inflammatory process	x	x	x
Focus group	Qualitative analysis		x	x

*Abbreviations: BES* Binge Eating Scale, *BPAAT* Brief Physical Activity Assessment Tool, *DEBQ* Dutch Food Behaviour Questionnaire, *EAT-26* Eating Attitude Test, *FFQ* Food Frequency Questionnaire, *HADS* Hospital Anxiety and Depression Scale *HbA1c* glycated haemoglobin, *MAAS* Mindful Attention Awareness Scale, *SCS* Self-Compassion Scale, *T1* 8 or 10 weeks post-intervention (TAU, TAU + MBHP, TAU + MB-EAT), *T2* 3 months post-intervention (TAU, TAU + MBHP, TAU + MB-EAT), *US-CRP* Ultra-sensitive C-reactive protein, *BDNF* Brain-derived neurotrophic factor, *TGL* Triglycerides

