As an attempt to improve adherence to the programme, all groups will receive an invitation to a monthly maintenance session (according to each protocol after the end of the programme, at 8 or 10 weeks) in addition to weekly emails with suggestions regarding formal and informal practices. Adherence to mindfulness practices by groups G2 and G3 will be evaluated at T1 and T2 with an appropriate form. Attendance will be monitored at each session; any individual who has not participated in at least half + 1 of the programme’s total sessions will be considered a loss to dropout. Each week the participants will be invited to keep a practice journal, and average practice at home, type of practice, frequency and so forth will be verified in their own form in the post-intervention evaluation and follow-up.

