#### Biochemical analysis

All tests (fasting blood glucose, haemoglobin A1c, insulin, total cholesterol, fractions and triglycerides, serum cortisol and ultra-sensitive C-reactive protein will be performed and samples collected between 7 and 9 a.m. according to the procedures described by the São Paulo Municipal Health Department [49] at each of the BHUs participating in the research. Brain-derived neurotrophic factor (BDNF) will be measured using the enzyme-linked immunosorbent assay method. BDNF has been associated with various aspects of plasticity in the brain. Stress-induced remodelling of the cortex, hippocampus and amygdala coincides with changes in BDNF levels. It is known that some forms of mindfulness meditation training can reduce stress-induced cortisol secretion, which could have neuroprotective effects by increasing levels of BDNF [50]. Samples for alpha-1-glycoprotein analysis (marker of inflammation) will be collected at baseline and at 8 or 10 weeks (according to the type of intervention) as well as 3 months post-intervention at the outpatient clinic of the Universidade Federal de São Paulo on the same day as completion of psychometric scales, food consumption and body composition evaluations. In addition to the quantitative analysis, this study will include qualitative evaluation; data will be gathered from focal groups, with open-ended questions about the expectations of the programme, the viability and implications in an everyday context, and changes in eating behaviour after the end of the intervention.

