### Analysis plan

#### Primary outcome measures

The primary outcome variables are those indicating improvement in eating behaviour. Self-report instruments to be used to track eating behaviour are the DEBQ and the BES, collected from T0 to T2.

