### Data analysis

The qualitative variables will be described as numbers and percentages, and quantitative data will be summarised as mean values with SD if the assumption of normality of data has been satisfied; otherwise, the median and 25% and 75% percentiles will be used. The three conditions for the treatment will be compared with baseline measures to evaluate the success of randomisation. In this case, the chi-square test or Fisher’s exact test for qualitative variables will be used, and one-way ANOVA or the Kruskal-Wallis test will be applied for quantitative variables.

Longitudinal data (T0, T1 and T2) will be collected for each group, which means that they will not be independent; therefore, repeated-measures ANOVA will be used. When assessing the effectiveness of the TAU programme, repeated-measures ANOVA will be used to assess the main effects of time and treatment, and the interaction between them. The analysis will be performed with the complete sample, and we plan to perform analyses in subgroups stratified by BMI. The models will be adjusted for possible confounding variables, such as age, BMI and other relevant covariates. Differences will be identified by using test linear hypotheses after ANOVA, and multiple testing will be adjusted by the Bonferroni correction.

The data will be evaluated for the intention-to-treat analysis; that is, the analysis will include all participants after randomisation. For the per-protocol analysis, women in the intervention groups who do not participate in at least four sessions will be excluded. For the attrition analysis, we will compare women who complete the protocol with women who answered only the baseline questionnaire.

All data analysis will be performed with STATA version 14.2 software (StataCorp, College Station, TX, USA) [58]. *p* Values < 0.05 will be considered statistically significant. No datasets were generated or analysed during the present study.

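### The protocol gives the T1 primary questionnaires at the last class, against its own T1 definition and clinic day, which risks attendance-related missing T1 data in the programme arms

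*Protocol article*

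**What the plan says.** The protocol article speaks to T1 collection in several places.

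- **Primary outcome measures.** "Self-report instruments to be used to track eating behaviour are the DEBQ and the BES, collected from T0 to T2".
- **Follow-up assessments, timing.** The evaluations after baseline occur "immediately after the 8- or 10-week intervention (T1) and at 3 months post-intervention (T2").
- **Follow-up assessments, administration.** A later sentence of the same paragraph says "the questionnaires will be administered before the beginning of the first and last sessions of each group, as well as at follow-up".
- **Biochemical analysis.** The alpha-1-glycoprotein sample is taken at baseline, at 8 or 10 weeks and at 3 months, "at the outpatient clinic of the Universidade Federal de São Paulo on the same day as completion of psychometric scales".
- **Recruitment.** "any individual who has not participated in at least half + 1 of the programme’s total sessions will be considered a loss to dropout".
- **Data analysis.** The intention-to-treat statement is that "the analysis will include all participants after randomisation". A per-protocol analysis and an attrition analysis are planned separately.

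Table 2 lists 8 MBHP sessions and 10 MB-EAT sessions. The TAU section describes usual care in the health units, with group activities as an option and no course that has a last session.

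**The concern.** Outcome collection in a randomised trial should not depend on adherence to the allocated treatment. If DEBQ and BES at T1 are completed by those who come to the last class, a woman who has left MBHP or MB-EAT is likely to have no T1 value. TAU women have no such class and need another route. Missingness could then differ between the arms for a reason tied to treatment and possibly to outcome.

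The first hypothesis compares a programme added to TAU with TAU alone on eating behaviour, and T1 is one of the two time points after baseline in that comparison. An analysis plan can adjust for some of the loss, but it cannot supply T1 questionnaires that were never sought.

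**Working it through.** **The passages side by side**

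1. *Within Follow-up assessments.* One sentence puts T1 after the 8- or 10-week programme. The other gives the questionnaires before the last session starts, so before the programme is complete.
2. *Follow-up assessments against Biochemical analysis.* The first links the questionnaires to a class. The second links them to a clinic day, and nothing ties that day to class attendance.
3. *By arm.* Only MBHP and MB-EAT have a described last session. The abbreviations under Table 1 nevertheless list T1 for all three arms.
4. *Dropout rule.* The half-plus-one rule can be met only by women who have a programme. It labels them as lost but does not say whether their outcomes are still sought.
5. *Contact with absentees.* Emails go to women who miss sessions without giving a reason. The stated purpose is to encourage practice, not to collect outcomes.
6. *T2.* The same sentence places it at follow-up, with no class attached.

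The route a site follows therefore decides who has a T1 primary outcome.

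**Planned size**

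Inputs from Participants and setting: f = 0.25, 5% significance, 80% power, about 20% dropout. With d = 2f = 0.5, a two-sided two-group t test needs 64 per group. Then 64 / (1 − 0.20) = 80 per group, and 3 × 80 = 240. The stated total reproduces on this basis, and the concern does not dispute it. Loss of power is not the issue either: with 64 against 80 women, power at d = 0.5 is 84%. The dropout allowance protects numbers, but it does not protect against selective loss.

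**Illustration of bias**

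Let p be the share of an arm missing at T1, and g the amount, in SD units, by which the missing women do worse than those measured. The measured mean then differs from the full-arm mean by p × g. For a programme against TAU, using observed T1 values only:

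bias = p(programme) × g(programme) − p(TAU) × g(TAU)

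Inputs: p(programme) = 0.20, which is the protocol's overall dropout figure placed in a programme arm by assumption. p(TAU) = 0, an assumption. g = 0.2 to 0.4, an assumption with no source in the protocol.

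| Case | Calculation | Bias (SD) | Share of d = 0.5 |
|---|---|---|---|
| g = 0.2, no TAU loss | 0.20 × 0.2 | 0.04 | 8% |
| g = 0.4, no TAU loss | 0.20 × 0.4 | 0.08 | 16% |
| g = 0.4 in both arms, 10% TAU loss | 0.08 − 0.10 × 0.4 | 0.04 | 8% |
| g = 0.4 in both arms, 20% TAU loss | 0.08 − 0.20 × 0.4 | 0 | 0% |

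If women leave for reasons unrelated to eating behaviour, g = 0 and there is no bias. If leavers do better, the sign reverses.

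**The case against.** The strongest reply is that the administration sentence says when questionnaires are given, not who is excluded. Nowhere does the protocol say that an absent woman goes unmeasured. The clinic visit offers a route independent of attendance, the intention-to-treat statement covers everyone randomised, and procedures for reaching women who miss a visit are commonly left to the full protocol. All of this stands. The absence of a retrieval procedure is not the point here. The point is a stated collection rule that conflicts with two other statements.

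A reader might go further and infer that women who stop attending give no T1 outcome, that this happens in the programme arms only, and that T1 compares class attenders with all TAU women. The documents do not support that:

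- The clinic-day passage may be the operative one.
- TAU women can also be lost, and the 20% is not split by arm.
- A woman who missed earlier classes but comes to the last one is measured.

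Nor is it shown that no model could help. Attendance is recorded at each session, baseline is measured, and T2 is collected outside the classes, so some of the loss may be explained by observed data.

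**Conclusion.** The concern holds as a contradiction with a real risk attached. The protocol gives incompatible accounts of when and where the T1 primary questionnaires are completed. One of them, if followed, makes a T1 outcome depend on class attendance in MBHP and MB-EAT. That fits poorly with an analysis of all randomised women. T2 does not share the problem.

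Size and direction are not known from the document. The 0.04 to 0.08 SD rests on three assumptions: the whole 20% loss falls in a programme arm, TAU loses nobody, and leavers are 0.2 to 0.4 SD worse. Similar loss in TAU shrinks the bias.

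A reader might also infer a demonstrated bias in favour of the programmes, or turn the illustration into a false-positive rate. An unadjusted z test at T1 with 64 against 80 women and 0.08 SD of bias has SE = √(1/64 + 1/80) = 0.168 and rejects in 7.6% of trials instead of 5%. That is not the planned test, which is a covariate-adjusted repeated-measures ANOVA over three time points with Bonferroni-corrected contrasts. The figure should not be quoted as the error rate of this trial.

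**What to change.** Reconcile Follow-up assessments with Biochemical analysis:

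- Remove the last session as the means of collecting the T1 questionnaires.
- State that DEBQ and BES at T1 are sought from every randomised woman, whether or not she still attends, at the university clinic visit in all three arms.
- If there is a fallback for women who do not come, use the same self-completed format and offer it equally in all arms. Telephone completion used mainly for non-attenders would mix mode of administration with adherence.
- State that the half-plus-one rule describes adherence and does not end outcome collection.

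The cost is wording and a modest number of extra contact attempts. If 20% of a programme arm were absent, that is 0.20 × 80 = 16 women per arm. The clinic visit is already planned at all three time points, and TAU women need a route outside the classes in any case. The change is worth making while T1 collection is still under way, because a missed T1 questionnaire cannot be collected later.

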### Interventions

#### TAU

According to nutritional status, overweight or obesity, as well as the presence of co-morbidity, different actions can comprise the treatment offered in PC [1]. For individuals presenting with overweight (BMI 25–29.9 kg/m^2^) but with no co-morbidities, PC teams at the different BHUs will organise care plans to enable them to achieve a normal BMI range (BMI 18.5–24.9 kg/m^2^).

Aside from the participants’ inclusion in group activities, for those who have co-morbidities such as hypertension and diabetes, individual dietary prescriptions will be offered by a nutritionist if deemed necessary. This decision will be discussed between the PC and matrix support teams.

For treatment of obesity (BMI 30–40 kg/m^2^) with or without co-morbidities, PC teams from the corresponding BHUs and matrix support teams must assess the need for the provision of behavioural therapy and pharmacotherapy, and must organise it, when appropriate, because these are usually provided within the PC system. Group activities can be offered to promote healthy eating and physical exercise. The more complex cases or cases with a BMI ≥ 40 kg/m^2^ will be assisted by specialised services (ambulatory or hospital setting).

The MBHP and MB-EAT groups will be led by a researcher who has experience in both protocols and specific meditation training and practice. The MBHP group will have a minimum of 8 participants and a maximum of 20; the MB-EAT group will have between 8 and 15 participants.

#### Mindfulness-Based Health Promotion + TAU

Our research groups (in Brazil and Spain) developed a general MBI that is an 8-week programme called Mindfulness-Based Health Promotion (MBHP) [51]. It is based on the original model developed by Kabat-Zinn et al. (mindfulness-based stress reduction [MBSR]) [52, 53] and subsequently adapted by our research group to better fit the context and needs of PHC as well as the local and national health systems [54]. It has been applied by the “Mente Aberta” Centre in Brazil (www.mindfulnessbrasil.com) and by the University of Zaragoza in Spain (www.webmindfulness.com). The sixth of these sessions is conducted in silence for the purpose of deepening the practice of mindfulness [51] and is similar to the MBSR retreat day session, but it is adapted to make it more feasible to implement in health centres and facilities. This more didactic and clearer sequence of the content helps improve the training of PHC providers, such as mindfulness teachers, enabling them to offer the programme to patients independently (cascading effect) [51].

As with MBSR, participants receive suggestions for activities to be performed at home or in the workplace on a regular daily basis, aiming for 15 to 20 minutes of practice, on average, and up to 45 minutes if possible (for those who are more engaged and motivated). They are also encouraged to bring the experience of mindfulness into their daily lives (informal practices). The main mindfulness practices used are mindfulness of breathing, mindfulness of the body (body scan), mindful walking and mindful movements (in which gentle physical movements are used), which can be practised by people with different levels of physical capacity. In addition to the MBSR protocol, the MBHP introduces a few dynamic activities to gain better insight into the concepts developed in the psychoeducational part of the programme, such as the “first and second suffering” and “hi-thanks-goodbye” practices; the practice of kind awareness (addressing equanimity and interpersonal aspects, based on Buddhist practices of compassion and self-compassion); and the 3-minute breathing space practice of mindfulness (from the mindfulness-based cognitive therapy protocol) [55]. The two last practices are adapted from the Breathworks Institute protocol [56].

#### MB-EAT + TAU

Inspired by the MBSR programme and eating-related research, MB-EAT was initially developed for individuals with compulsive eating problems and obesity [57]. The programme includes the four main techniques of meditation mentioned in the MBHP programme. In addition, mindfulness is applied to various aspects of the participants’ eating behaviour and to their experience of inner wisdom and outer wisdom. Every session also includes mindfulness practices for the cultivation of a greater awareness of hunger, fullness, taste awareness with different foods, and triggers for overeating. Overall, a greater sense of self-awareness and self-acceptance regarding eating and weight is cultivated. The specific elements of each session in both programmes are described in Table 2.

**Table 2 Tab2:** Content and formal practices of each session of MBHP and MB-EAT

Program	MBHP	MB-EAT
session		
1	What is mindfulness? *Formal practices:* -Eating a raisin -Body scan	Internal and external wisdom *Formal practices:* - General mindfulness meditation - Eating four raisins - Introduction to a general mindfulness practice
2	Mindfulness in breathing *Formal practices:* -Mindfulness while breathing -Body scan	Mini-meditations, eat consciously and food calories (smart changes) *Formal practices:* - General mindfulness meditation - Introduction to mini-meditations (10 min) - How to read labels and the nutritional composition of products - Mindfully eating high-fat food: cheese and crackers
3	Mindfulness in the body (part I) *Formal practices:* -Mindful walking -Mindfulness while breathing	Mindfulness while breathing Awareness of physical hunger, awareness of body and emotional eating *Formal practices:* - Longer meditation practice - Hunger awareness self-rating practice - Body scan
4	Mindfulness in the body (part II) *Formal practices:* - Mindful movements - Mindfulness while breathing, sensations, sounds and thoughts - 3-Min breathing space in pairs - Mindful walking	Physical activity, satisfaction of taste and self-healing touch *Formal practices:* - General mindfulness meditation - Taste satiety exercise with chocolate food - Healing self-touch
5	Mindfulness and acceptance *Formal practices:* - Mindful movements - Mindfulness of thoughts - 3-Min breathing space in doubles	Awareness of fullness, conscious choices and forgiveness *Formal practices:* - General mindfulness meditation - Stomach fullness and body satiety - Making mindful choices: cookies and chips - Emotional eating, anger and forgiveness meditation
6	Silence *Formal practices:* - Mindful movements - Body scan - Mindfulness while breathing - Mindful walking	Integrating internal and external wisdom: becoming conscious about nutrition and energy balance *Formal practices:* - Mindful eating choices exercise: fruits and veggies - Integrated mindful eating meditation
7	Compassion *Formal practices:* - Metta (for oneself and others) - Mindfulness while breathing - Mindful movements	Eating, conscious choices and community meal *Formal practices:* - Brief meditation practice - Mindful choice/taste awareness meditation - Mindful eating: potluck meal
8	Mindfulness for life *Formal practices:* - Metta (for oneself and others) - Mindfulness poem	Conscious movement and emotions *Formal practices:* - Mindfulness meditation - Body scan - Trigger meditation - Craving meditation - Walking meditation
9		Stress, suffering, eating and values: working with thoughts and emotions *Formal practices:* - Mindfulness meditation - My favourite food exercise
10		Breaking the chain, connecting to yourself and moving on *Formal practices:* - Meditation practice - Experience of sitting meditation - Wisdom meditation - Shared celebration/eating

Both the MBHP and MB-EAT programmes also assign practices to be used at home during the week, including mindfulness-based meditation and eating-related practices for MB-EAT. Emails will be sent to participants after each session, encouraging them to engage in the practice of the week, as well as to those who fail to provide reasons for their absence from the programme. The monthly maintenance sessions offered may stimulate continued practice at home by participants in groups G2 and G3.

### Analysis plan

#### Primary outcome measures

The primary outcome variables are those indicating improvement in eating behaviour. Self-report instruments to be used to track eating behaviour are the DEBQ and the BES, collected from T0 to T2.

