##### Dutch Food Behaviour Questionnaire

The Dutch Food Behaviour Questionnaire (DBEQ) is a self-applied questionnaire validated by Wardle [26] and adapted and translated into Portuguese by Almeida [27]. The questionnaire comprises 33 items assessed on a scale of 5 points (never=1, rarely=2, sometimes=3, often=4, very often=5), spread across three scales: the scale of restriction includes 10 items; the external intake range also consists of 10 items; and the scale of emotional intake consists of 13 items.*Restricted food intake*: the participants’ eating style and knowledge of nutritional habits and the effort they regularly exert to control their appetite and food intake.*Emotional eating*: related to the person’s emotional state, it represents the loss of control over food intake due to exposure to factors of emotional stress, which results in food disinhibition.*Food intake due to external factors*: eating influenced by how attractive the flavour and taste of food is; it will represent the disinhibition or loss of control that occurs due to external factors intrinsic to the food available or the social situation in which they are offered.

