##### Binge Eating Scale

The Binge Eating Scale (BES) is a self-applied questionnaire developed by Gormally et al. [28] that is widely used in English-speaking countries and has been translated into Portuguese for use in Brazil by Freitas et al. [29]. It shows how to appropriately discriminate obese individuals according to the severity of their binge eating. It consists of a list of 16 items assessed on a Likert scale. Every statement matches a number from 0 to 3 points, ranging from the absence (“0”) to the maximum severity (“3”) of binge eating. The final score is the result of the sum of the points for each item. Scoring is as follows: ≤ 17 = normal; 17–30 = variation in tendency to eat a lot (anything really); ≥ 30 or more = binge eating.

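### Four primary scores have no deciding score, visit or success rule, and the Bonferroni sentence does not say whether it covers the scores

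*Protocol article*

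**What the plan says.** - **Primary outcome** (Primary outcome measures): "The primary outcome variables are those indicating improvement in eating behaviour". The next sentence names the instruments: "Self-report instruments to be used to track eating behaviour are the DEBQ and the BES, collected from T0 to T2".
- **DEBQ** (Dutch Food Behaviour Questionnaire): the items are "spread across three scales", namely restriction, external and emotional eating. No total is described.
- **BES** (Binge Eating Scale): "The final score is the result of the sum of the points for each item". This is one score.
- **Visits** (Follow-up assessments, Table 1): baseline (T0), end of programme (T1) and three months later (T2). Neither follow-up visit is named as primary.
- **Model** (Data analysis): "repeated-measures ANOVA will be used to assess the main effects of time and treatment, and the interaction between them".
- **Multiplicity** (Data analysis): "Differences will be identified by using test linear hypotheses after ANOVA, and multiple testing will be adjusted by the Bonferroni correction". The general significance threshold is 0.05.
- **Sample size** (Participants and setting): 240 women, 80 per group, at a 5% significance level and 80% power, for Cohen's f = 0.25 with about 20% dropout. The 5% is not divided.

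**The concern.** Three DEBQ scales and the BES total make four primary scores. The protocol does not say whether success needs any one of them, all of them, or a fixed order of testing. The hypotheses that a mindfulness programme improves eating behaviour, that the targeted programme beats the general one, and that the general one changes eating behaviour all refer to the construct and not to a score. Each could therefore be declared supported on whichever score reaches significance.

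The Bonferroni sentence does not settle this. It follows the clause on linear hypotheses after ANOVA, so its most natural scope is the set of contrasts within one score's model. On that reading nothing holds 5% across the four scores. On the wider reading the error is controlled, but the sample size was not set for it.

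Choosing the primary variable is a protocol matter. The article has a section for it, and that section does not identify which variable decides.

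**Working it through.** **Reproducing the plan's 240.** A two-group F test with f = 0.25 (a difference of 0.5 SD) at two-sided 5% and 80% power needs 64 per arm. Then 64 / (1 − 0.20) = 80 per arm, and 3 × 80 = 240. The stated figure is matched exactly on a pairwise basis at an undivided 5%. The three-group repeated-measures calculation that the article names does not give 240; that is a separate matter. The pairwise basis is used below only because it matches.

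**Counting the scores.** DEBQ 3 + BES 1 = 4. T0, T1 and T2 enter one repeated-measures ANOVA per score, so there is one group-by-time test per score, four in all.

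**Reading A: Bonferroni acts only within each score's ANOVA.**

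For four independent tests at 5%: 1 − 0.95⁴ = 0.185.

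The documents give no correlation between the scores, so a range is assumed. Null trials were simulated with 3 arms of 64, visit correlation 0.5 and four scores with a common correlation. The six contrasts per score are three pairs of arms at each of two visits. Chance of at least one false-positive score:

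| Criterion | Range for correlation 0.7 to 0 |
|---|---|
| Group-by-time F test at 5% | 13–19% |
| Any Bonferroni-adjusted contrast within a score, no F test required | 12–16% |
| Significant F test and an adjusted contrast | 8–12% |
| Same, improvement direction only (lower assumed better on all four) | 4.6–6.2% |
| F test with Bonferroni across the four scores (0.0125 each) | 4–5% |

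The first three rows and the last count either direction. At 5% two-sided, the nominal share for one direction is 2.5%, so the fourth row is still inflated, though far less than the first might suggest.

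**Reading B: Bonferroni covers the four scores.**

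- Level per score: 0.05 / 4 = 0.0125. Family-wise error is at most 5%.
- Standardised difference with 64 per arm: 0.5 / √(2/64) = 2.83. Two-sided critical value at 0.0125: 2.50. Power = Φ(2.83 − 2.50) = Φ(0.33) ≈ 0.63. The F-test calculation gives 0.62.
- At an undivided 5% the same F-test calculation gives 0.80.
- Keeping 80% at 0.0125 needs 91 per arm. 91 / 0.80 = 113.75, so 114 per arm, and 3 × 114 = 342 women.

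Naming one score and one contrast keeps both the 5% and the 240 on this basis.

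**The case against.** The strongest reply is that the protocol does promise a Bonferroni correction, and that its wording does not exclude the scores. This stands: the family is undefined, not shown to be narrow, and if it includes the scores the error rate is held. It is also fair that the exact family and the order of contrasts are often left to an analysis plan, which is not shown here. The choice of deciding score is a different matter and belongs in the protocol.

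Some stronger readings are tempting, but the documents do not support them:

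- **Eight separate tests at 5%, four scores at two visits.** The visits enter one ANOVA per score and are not tested separately at 5%.
- **A false claim of improvement about three times as often as 5%.** The 13–19% counts differences in either direction and assumes that any one score suffices, a rule the protocol does not state. For improvement alone, after a significant F test, the figure is 4.6–6.2%.
- **Power lost to a correction over 24 tests (four scores, three pairs, two visits).** The protocol adopts no such rule, and its stated power is for main effects of group and time, not for contrasts.
- **Primary status assigned by result.** A reader might take the phrase about indicating improvement that way, but the next sentence names the DEBQ and BES in advance. It is loose wording, not a selection rule.

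**Conclusion.** The point holds in a limited form. The protocol fixes four primary scores without a deciding score, visit or success rule, and the scope of its multiplicity correction is open.

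Under the most natural reading, the chance of at least one false-positive score is about 13–19% by F test, or about 8–12% when an adjusted contrast is also required, in either direction. These figures rest on assumed correlations between scores of 0.7 to 0, an assumed visit correlation of 0.5, 64 evaluable women per arm, and a rule that any one score is enough.

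Under the wider reading, error is at most 5%, and the cost is power: about 62–63% for one score instead of 80%, for a 0.5 SD pairwise difference. So either the error rate across scores is not held at 5%, or the sample size does not match the correction. The text does not say which.

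**What to change.** Settle this before analysis, in the protocol, the registry entry and the analysis plan, by one of two routes:

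1. Name one primary score at one visit and make the other scores and the other visit secondary. Which score and visit is for the investigators to decide. The 5% level and the 240 women can stay. The cost is that the other scores lose primary status.
2. Keep all four scores primary, and state that Holm or Bonferroni is applied across them and what counts as success. Restate the power at the adjusted level: about 62–63% for one score under Bonferroni on the basis above. Keeping 80% on that basis would need 342 women.

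Under either route, say which contrasts form the Bonferroni family within a score, and replace the phrase about variables that indicate improvement with the names of the scores. The article reports that recruitment was still under way when the manuscript was submitted. The change is one of wording, plus a restated power figure under the second route.
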